## Assignment of interventions: blinding

### Who will be blinded {17a}

Due to the nature of the intervention, neither the patients nor the investigator can be blinded to the randomization allocation. The allocation data within the dataset will be presented as either ‘0’ or ‘1’, without the corresponding randomization allocation. Thereby, the investigator performing the analysis will be blinded to the randomization allocation.

### Procedure for unblinding if needed {17b}

Not applicable, neither participants nor investigators are blinded to the randomization allocation.

## Data collection and management

### Plans for assessment and collection of outcomes {18a}

Psychological well-being will be expressed as the presence and severity of PTSD, anxiety and depression, which will be assessed using the Impact of Event Scale-Revised (IES-R) and Hospital Anxiety and Depression Scale (HADS) [36, 37]. Quality of life will be assessed using the European Quality of Life 5-dimensions (EQ-5D) and RAND-36 questionnaires [38, 39]. Patients’ satisfaction with and rating of ICU care and aftercare and patients’ perspectives on ICU-VR will be assessed using a novel questionnaire.

The IES-R comprises 22 items, assesses subjective distress caused by a traumatic event and has been previously validated in ICU survivors [40]. The IES-R yields a total score (ranging from 0 to 88, with higher scores indicating more severe symptoms), and subscale scores can be calculated for symptoms of intrusion, avoidance and hyperarousal. An IES-R sum score ≥ 24 will be considered as PTSD [41]. The HADS comprises 14 items and is commonly used to determine the levels of anxiety and depression that a patient is experiencing. Seven of the items relate to anxiety and seven relate to depression. A sum score above 8 on either the depression or anxiety subscale will be classified as depression and anxiety, respectively [36].

The EQ-5D measures quality of life in five dimensions (mobility, self-care, usual activities, pain/discomfort and anxiety/depression), from which the weight of a health state can be computed, the EQ-5D utility score, ranging from − 0.446 (worst quality of life) to 1.000 (best quality of life) [42]. Additionally, patients score their current subjective health on a visual analogue scale (EQ-VAS), ranging from 0 (worst health imaginable) to 100 (best health imaginable). The RAND-36 is a 36-item, patient-reported survey of patient health and quality of life. The RAND-36 consists of eight scaled scores, which are the weighted sums of the questions in their section. Each scale is directly transformed to a scale ranging from 0 to 100 on the assumption that each question carries an equal weight. The eight sections are vitality, physical functioning, bodily pain, general health perception, physical role functioning, emotional role functioning, social role functioning and mental health [39].

Patients’ satisfaction with and rating of ICU care and aftercare was based on the Patient Satisfaction Questionnaire and Family Satisfaction with ICU Care tools, altered to the needs of this study [43–45]. Additional novel items were added to evaluate patients’ perspectives on the ICU-VR intervention.

This questionnaire comprised 21 items, categorized in four sections: (1) satisfaction with and rating of ICU care and ICU aftercare and the added value of ICU-VR; (2) overall perspectives on the ICU-VR intervention; (3) perspectives on the content of ICU-VR; and (4) perspective on the effect of ICU-VR. Questions regarding ICU-VR were only answered by patients who had received the intervention, questions regarding satisfaction and rating by all patients. Psychological well-being and health-related quality of life will be assessed at 3, 4, 6, 7 and 12 months after hospital discharge. Satisfaction with and rating of ICU care and aftercare and perspectives on ICU-VR were administered by telephone during the study period after the first outpatient clinic visit. Baseline demographics and treatment-related characteristics, including, but not limited to, age, gender, race, pre-existing comorbidities, hospital and ICU length of stays, mechanical ventilation-related data (duration, prone positioning, highest PaO_2_/FiO_2_ ratio, occurrence of delirium, sedation, illness severity scores (APACHE IV, SAPS II)), mortality and medication, will be retrieved from electronic patient records.

### Plans to promote participant retention and complete follow-up {18b}

Patients will be contacted by telephone when a questionnaire needs to be filled in to improve follow-up completion. If a participant decides to discontinue their participation, the reason for the discontinuation will be recorded.

### Data management {19}

Data will be uploaded, stored and maintained on the electronic data capture system of Castor EDC. The study team will be responsible for all data entry and quality control activities. The data will be checked by at least two persons from the study team and will be stored for at least 15 years on either the Castor EDC server or as a hardcopy in the ICUs of the participating hospitals. Questionnaires will preferably be sent digitally using either Castor EDC or Gezondheidsmeter PGO+ (Gezondheidsmeter, Amsterdam, the Netherlands). The latter is an online CE-certified system to digitally monitor patients and is used by all the hospitals participating in the COVID-19 aftercare programme. Patients who are unable to fill out the questionnaires online will receive hardcopy questionnaires by postal mail.

### Confidentiality {27}

To maintain anonymity, collected data will be coded with a code number, and this number will be the only reference to patient identification throughout the study. The principal investigator is the only one in possession of the translation key, making it impossible to link data to the patient. Informed-consent forms will be kept in a locked cabinet in a limited-access room at the Erasmus MC. Patient data will be stored on each local hospital’s secured server, and only the local researcher will have access to the data files, which will be stored independent of the allocation data. Data will be archived for 15 years. The handling of personal data complies with the Dutch law.

### Plans for collection, laboratory evaluation and storage of biological specimens for genetic or molecular analysis in this trial/future use {33}

Not applicable, no biological specimens were sampled.

## Statistical methods

### Statistical methods for primary and secondary outcomes {20a}

Baseline demographics and treatment-related characteristics will be quantified using descriptive statistics. Continuous variables will be presented as medians (95% range). Categorical variables will be presented as absolute numbers and relative frequencies.

Differences between study groups in continuous variables, such as the IES-R sum score, the HADS anxiety and depression scores, the RAND-36 subscales and the EQ-5D utility score, at several follow-up time points will be analysed using a mixed effect linear regression model with a random intercept for each study site. Patients will also be categorized based on clinically meaningful cut-offs for the IES-R sum score and the HADS anxiety and depression scores. An IES-R sum score ≥ 24 will be considered as clinically relevant PTSD; a HADS anxiety or depression score > 8 will be considered as clinically relevant anxiety or clinically relevant depression, respectively [36, 41, 46]. Differences in categorical variables between study groups at several follow-up time points will be analysed using a mixed effect logistic regression model with a random effect for each site. Differences in continuous or categorical variables throughout follow-up will be analysed using a mixed effect linear or logistic regression model with an interaction variable of time*randomization and a random intercept and/or slope for each individual and each study site as appropriate.

To determine whether there are time-specific windows of opportunity (3 or 6 months after hospital discharge) for the effect of ICU-VR, we will analyse psychological impairments and quality of life 1 month (4 and 7 months after hospital discharge in the early and late intervention groups, respectively), 3 months (6 and 9 months after hospital discharge in the early and late intervention groups, respectively) and 6 months after receiving ICU-VR (nine and 12 months after hospital discharge in the early and late intervention groups, respectively) using mixed effect linear/logistic regression models with a random intercept for each site and an interaction variable time*randomization.

All data will be gathered using Castor EDC. All analyses will be performed using SPSS (version 24.0; SPSS Inc., Chicago, IL) and R for Statistics (R Foundation for Statistical Computing, Vienna, Austria, 2015). A *P* value ≤ 0.05 will be considered statistically significant.

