### Participant timeline {13}

Figure 2 depicts participants’ recruitment and randomization, the study procedures and the outcomes of the study. Patients admitted for COVID-19 to the ICU of the participating hospitals will be invited to a post-COVID-19 outpatient clinic 3 months after hospital discharge as part of the regional standard of care. All patients will receive an information letter and will be contacted by telephone to discuss participation 1 month prior to this visit. During the outpatient clinic visit, informed consent will be obtained and patients will be randomized. Patients randomized to the early ICU-VR group will receive ICU-VR during the same visit, whereas patients randomized to the late ICU-VR group will receive ICU-VR during a second outpatient clinic visit 3 months later (i.e. 6 months after hospital discharge). Questionnaires will be sent at 3 months (prior to the first outpatient clinic visit), 4 months, 6 months (prior to the second outpatient clinic visit for patients in the late intervention group), 7 months and 12 months after hospital discharge.

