### Sample size {14}

In the previously conducted pilot study examining the feasibility, safety and clinical relevance of ICU-VR in sepsis survivors, we identified an effect size Cohen’s *d* of 0.77 [33]. Due to the non-normality of PTSD scores after 6 months, these calculations could represent an overestimation of the sample size. We consider the effect estimates for the ICU-VR module to be similar to the intervention group, as was tested in our pilot study. A G*Power analysis revealed that 80 patients have to be included in the study to detect such an effect size, using a two-sided alpha of 0.05, a power of 0.80, a 1:1 randomization and an expected loss to follow-up of 20% based on our pilot study. We will include patients from June 2020 to December 2020. When the minimum required number of patients is reached prior to December 2020, inclusion will be continued until December 2020. When the minimum required number of patients is not reached in December 2020, inclusion will be continued until the minimum required sample of 80 patients is reached.

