## Assignment of interventions: allocation

### Sequence generation {16a}

Patients will be randomly assigned to either early ICU-VR, receiving the intervention 3 months after discharge, of late ICU-VR, receiving the intervention 6 months after hospital discharge. Randomization will be a 1:1 allocation as per computer-generated randomization schedule stratified by site using permuted blocks of random sizes. The block sizes will not be disclosed, to ensure concealment.

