### Limitations

There are some limitations to our study design. First, as our previous research has only revealed the effect of ICU-VR offered in the first weeks after ICU discharge, we had to assume a comparable effect size when delivered 3 months after discharge. This may increase the risk of a type II error. To minimize this risk, we decided to include in pre-specified time period, and inclusion will be continued in case our enrolment aim is reached within this period. Furthermore, as the outcome variables were not normally distributed in our previous study, we did not assume any distribution, which may have resulted in an overestimation of our required sample size. Second, the generalization of results from this study may be limited because patients were only included at four different hospitals in a confined area in the Netherlands. Third, as we believe that the effect of our intervention is partially dependent on exposure to the actual environment where a patient was treated, we used hospital-specific ICU-VR, limiting easy implementation in other hospitals. Last, due to the nature of the intervention, neither investigators nor participants could be blinded to patients’ allocation. To reduce this bias, analysation will be conducted blind.

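### The group comparisons at single follow-up times are specified without the 3-month pre-randomisation score, so precision available from data already being collected is given up

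*Protocol article*

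**What the plan says.** The section on statistical methods for primary and secondary outcomes {20a} states that differences between groups in the IES-R, HADS, RAND-36 and EQ-5D scores "at several follow-up time points will be analysed using a mixed effect linear regression model with a random intercept for each study site". Outcomes dichotomised at the cut-offs get a logistic counterpart with a random site effect. The same section then describes another model, for differences over the whole of follow-up. It has a time-by-randomisation interaction and random effects for patient and site as appropriate.

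On timing, Participant timeline {13} says "Questionnaires will be sent at 3 months (prior to the first outpatient clinic visit" and places consent and randomisation at that visit. Plans for assessment and collection of outcomes {18a} gives psychological well-being and quality of life the same schedule: 3, 4, 6, 7 and 12 months. Each score therefore has a planned pre-randomisation value.

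Randomisation is stratified by site only: "Randomization will be a 1:1 allocation as per computer-generated randomization schedule stratified by site using permuted blocks of random sizes". Under Limitations the authors write that "we had to assume a comparable effect size when delivered 3 months after discharge" and accept that this may raise the risk of a type II error.

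**The concern.** The time-point models are described by their random site term, and no fixed covariate is named. The 3-month value of the same instrument is an obvious candidate predictor of the later value, and it cannot have been affected by allocation. Leaving it out keeps in the residual all the between-patient variation that it could explain. It also leaves any chance difference between the arms at 3 months in the estimate.

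This trial has reason to want the precision. Its effect size comes from a pilot in which the intervention was given much earlier, and its stated protection against a smaller true effect is to keep enrolling to the end of the recruitment period. Baseline adjustment addresses the same risk without further patients.

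**Working it through.** **Inputs from the documents.** Sample size {14} gives d = 0.77, "using a two-sided alpha of 0.05, a power of 0.80, a 1:1 randomization". It allows for 20% of patients being lost and arrives at 80 patients.

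**Assumed inputs.** The documents report no correlation r between the 3-month and follow-up scores, so r = 0.3, 0.5 and 0.7 are shown. A true effect of d = 0.5 is also an assumption, standing for an effect smaller than the pilot's.

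**Step 1: the plan's own figure.**
- Two-sample t test at d = 0.77: 28 per arm, 56 in total, 56/0.8 = 70.
- Wilcoxon-Mann-Whitney test with the minimum asymptotic relative efficiency of 0.864, which assumes no distribution: 32 per arm, 64 in total, 64/0.8 = 80.

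The second matches the stated 80 exactly and fits the remark under Limitations that no distribution was assumed. The sample size is reproduced, and 32 evaluable patients per arm is the right basis for what follows.

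**Step 2: variance.** With the 3-month score as a linear covariate, residual variance is multiplied by 1 − r². The 64 evaluable patients then carry the information of 64/(1 − r²) unadjusted patients.

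| r | 1 − r² | Reduction | Equivalent unadjusted patients |
|---|---|---|---|
| 0.3 | 0.91 | 9% | 70 |
| 0.5 | 0.75 | 25% | 85 |
| 0.7 | 0.51 | 49% | 125 |

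The reduction at r = 0.7 is 1 − 0.51 = 49%; 51% is the variance that remains.

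**Step 3: power.** Non-central t with non-centrality d/√(1 − r²) × √(32/2) = 4d/√(1 − r²), two-sided 0.05, with 62 degrees of freedom unadjusted and 61 adjusted. For d = 0.5 the non-centrality is 2.00 unadjusted, and 2.10, 2.31 and 2.80 at r = 0.3, 0.5 and 0.7.

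| True effect | Unadjusted | r = 0.3 | r = 0.5 | r = 0.7 |
|---|---|---|---|---|
| d = 0.77 | 85.8% | 88.8% | 93.8% | 98.9% |
| d = 0.5 | 50.4% | 54.1% | 62.3% | 78.7% |

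The effect detectable with 80% power, by normal approximation, is (1.96 + 0.84) × √(1 − r²) × √(2/32). That is 0.70 SD unadjusted, and 0.67, 0.61 and 0.50 SD at the three correlations.

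**Step 4: chance imbalance.** With 32 per arm, the standard error of the difference at 3 months is √(2/32) = 0.25 SD. A difference larger than that, in either direction, arises in about one trial in three. If r = 0.6, an imbalance of 0.25 SD moves the unadjusted follow-up difference by 0.6 × 0.25 = 0.15 SD.

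**Step 5: does the longitudinal model already do this?** Suppose 3 months is in the response and each arm has its own 3-month mean. The interaction then compares changes from 3 months. With one baseline, one follow-up and equal variances, the variance relative to the unadjusted comparison is 2(1 − r):
- r = 0.3: 1.40, against 0.91 for covariate adjustment
- r = 0.5: 1.00, against 0.75
- r = 0.7: 0.60, against 0.51

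That form is worse than no adjustment at r = 0.3, no better at 0.5, and obtains most of the gain at 0.7. If 3 months is not in the response, the score is not used at all. The article does not say which applies.

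**The case against.** The strongest reply is that the article describes the random-effects structure and lists no fixed effects, so its silence is not a decision against adjustment; covariates are often left to a fuller document. That stands in part: the article does not exclude the 3-month score, and nothing here shows that its omission was deliberate. But the section does specify its models, distinguishing site-only terms from patient-level ones, and as written the time-point models lack the covariate.

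A second reply is that the time-by-randomisation model may use the 3-month score. This also stands in part. A reader might infer that no analysis in the plan draws on the 3-month score; the documents do not support that. They leave it open, and they do not say which model carries the primary outcome. The point is therefore confined to the time-point comparisons, plus the observation that the longitudinal model does not secure the gain.

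Third, the size depends on undocumented inputs. That is correct. A strong within-patient correlation cannot be taken from the documents, and at r = 0.3 the gain is only about 3 to 4 percentage points of power. At the planned effect the trial meets its 80% target without adjustment. The power figures rest on normal theory, whereas the authors report non-normal scores. Thirty-two per arm is a planning figure, since enrolment may go beyond 80. The 3-month questionnaires are sent to patients, which does not guarantee that all are completed.

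Finally, in a logistic model, adjustment changes the odds ratio from marginal to conditional with respect to the 3-month score. It is therefore not purely a gain in precision, and no figure is claimed for those models.

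**Conclusion.** The point holds as a weakness in efficiency. The comparisons at single follow-up times are specified without the pre-randomisation score of the same instrument, and the longitudinal model is not specified in a way that makes up for it.

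Over an assumed r of 0.3 to 0.7 with 32 evaluable patients per arm, residual variance would fall to between 91% and 51% of its unadjusted value. The benefit is modest at the planned effect and low r. It is largest if the true effect is smaller than the pilot's, the risk that the authors themselves raise.

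A reader might infer that the planned comparisons are biased. They are not: randomisation makes the unadjusted difference valid on average, and the cost is lower precision plus an uncorrected imbalance in the particular sample obtained. Nor does the point show an error in the sample size, which reproduces exactly.

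**What to change.** In the statistical methods section {20a}, add one sentence stating that each linear model at a single follow-up time includes the 3-month value of the same continuous score as a fixed covariate, together with site. Alternatively, specify a longitudinal model with categorical time, the 3-month value in the response and a common 3-month mean across arms; this version also retains patients whose 3-month score is missing.

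For the dichotomised outcomes, adjust for the continuous 3-month score rather than its dichotomised form, and state that the resulting odds ratio is conditional on that score.

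The cost is analysis wording only, with no new data, visits or patients. Trial status describes data collection as ongoing, so the choice should be recorded before the outcome data are analysed by arm.

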## Methods: participants, interventions and outcomes

### Study setting {9}

This multicentre, randomized controlled, open-label trial will be conducted in the mixed-medical ICUs of four hospitals in Rotterdam, the Netherlands: one university hospital providing tertiary care (Erasmus MC) and three teaching hospitals providing secondary care (Franciscus Gasthuis & Vlietland Hospital, Ikazia Hospital and Maasstad Hospital).

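### The longitudinal model names only a random intercept and/or slope per patient for visits 1 to 9 months apart; if within-patient correlation fades with time, its standard errors of change are misstated, most of all with an intercept alone

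*Protocol article*

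**What the plan says.** The section Statistical methods for primary and secondary outcomes {20a} describes separate kinds of group comparison.

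- Continuous outcomes "at several follow-up time points will be analysed using a mixed effect linear regression model with a random intercept for each study site". No patient term is named there.
- Differences over the whole of follow-up use a mixed linear or logistic model "with an interaction variable of time*randomization" and "a random intercept and/or slope for each individual and each study site as appropriate".

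This point concerns the second model. The text does not say whether time is categorical or continuous, whether the slope is a straight line, or what the residual correlation is.

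The visit schedule is fixed in Plans for assessment and collection of outcomes {18a}: "Psychological well-being and health-related quality of life will be assessed at 3, 4, 6, 7 and 12 months after hospital discharge". Month 3 precedes the intervention. Outcomes {12} sets the primary outcome up to 6 months and places follow-up to 12 months among the secondary outcomes. Under Study setting {9} the trial "will be conducted in the mixed-medical ICUs of four hospitals in Rotterdam, the Netherlands".

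**The concern.** The time-by-arm interaction is a contrast of change, so its standard error depends on how strongly two visits in the same patient are correlated. A random intercept with independent residuals gives months 3 and 4 the same correlation as months 3 and 12. Adding a straight-line random slope lets correlation fall with distance, but describes each patient as a line plus independent noise. It therefore overstates the variance of change over one month when correlation fades gradually.

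Two things are at stake. Month 4 is the first assessment after early ICU-VR and lies in the primary window; too wide an error there costs power. With an intercept alone, too narrow an error at later visits produces too many false positives. Which of these occurs depends on a choice that the text leaves open.

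The same clause also permits a random slope across study sites, of which there are four.

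**Working it through.** **1. Numbers per arm.** Sample size {14} states "A G*Power analysis revealed that 80 patients have to be included in the study to detect such an effect size", with d = 0.77, two-sided alpha 0.05, power 0.80 and 20% loss. A t-test needs 28 per arm: 56 in total, and 56/0.8 = 70. That does not match. Limitations adds that "we did not assume any distribution, which may have resulted in an overestimation of our required sample size", which points to a Wilcoxon-Mann-Whitney calculation at the minimum asymptotic relative efficiency of 0.864. That gives 32 per arm, 64 in total, and 64/0.8 = 80, which matches. I use 32 evaluable per arm.

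**2. Assumed truth.** The documents give no correlations. I take correlation = (1 - g) × r^(months apart), with equal variances and complete data, and r from 0.93 to 0.97 and g from 0.05 to 0.15. Two settings span the results:

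| Setting | r, g | 1 month apart | 3 months | 9 months |
|---|---|---|---|---|
| A | 0.93, 0.05 | 0.883 | 0.764 | 0.494 |
| B | 0.97, 0.15 | 0.825 | 0.776 | 0.646 |

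**3. True standard error of the arm difference in change from month 3**, in SD units: √[(2/32) × 2(1 - ρ)]. At month 4:
- A: √(0.125 × 0.1165) = 0.121
- B: √(0.125 × 0.1755) = 0.148

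**4. Random intercept only.** With equal variances, the large-sample fit sets one common correlation equal to the mean, ρ̄, of the ten pairwise correlations (gaps 1, 1, 2, 3, 3, 4, 5, 6, 8 and 9 months): 0.713 in A and 0.750 in B. The ratio of model to true standard error is √[(1 - ρ̄)/(1 - ρ)], and the true size of a nominal 5% test is 2Φ(-1.96 × ratio).
- Month 4, A: √(0.2871/0.1165) = 1.57, size 0.2%. B: √(0.2497/0.1755) = 1.19, size 1.9%.
- Month 12, A: √(0.2871/0.5056) = 0.75, size 14%. B: √(0.2497/0.3538) = 0.84, size 10%.

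**5. Intercept only, fitted to months 3, 4 and 6** (one reading of the primary window). Now ρ̄ = 0.823 in A and 0.800 in B.
- Month 6, A: √(0.1769/0.2359) = 0.87, size 9.0%. B: √(0.2000/0.2242) = 0.94, size 6.4%.

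With a slope added, this three-visit fit is within about 3%.

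**6. Intercept plus linear slope, five visits.** The closest such covariance to the assumed truth was found numerically.
- Month 4, A: 0.1508/0.1207 = 1.25, size 1.4%. B: 0.1584/0.1481 = 1.07, size 3.6%.
- Months 6 and 7: ratios 0.93 to 0.98. Month 12: 1.02 to 1.03.

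A simulation of 600 trials per setting agreed: month-4 ratio 1.06-1.25 with intercept plus slope and 0.99-1.00 with an unstructured covariance.

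**7. Other patterns.** Steeper fading (0.95 down to 0.80 per month with no nugget) gives month-4 ratios of 1.65-1.93 for intercept only and up to 1.41 with a slope. Months 6 and 7 can then be up to 10% too narrow with a slope. If correlation is the same for all pairs, every ratio is 1.00. If the truth is a random slope, intercept plus slope gives 1.00 throughout.

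**8. Power at month 4**, Φ(effect/true SE - 1.96 × ratio):
- Effect 0.35 SD, A: 0.35/0.1207 = 2.90; 83% with a correct error, 67% with intercept plus slope. B: 0.35/0.1481 = 2.36; 66% against 61%.
- Effect 0.77 SD, intercept plus slope, A: 6.38 - 2.45 = 3.93. B: 5.20 - 2.10 = 3.10. Power is above 99% in both.

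**9. Site slopes.** A variance across four sites has three degrees of freedom. Even if each site's slope were known exactly, a 95% interval would run from 3/9.35 = 0.32 to 3/0.216 = 13.9 times the estimate.

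**The case against.** The strongest reply is that the article leaves open what is being criticised. It does not say that the slope is linear or that residuals are independent, and a residual correlation structure can accompany a random intercept. Such detail often sits in a full protocol or analysis plan, neither of which is shown. This stands in part: independence is inferred from the ordinary meaning of the terms. But the text does name a structure, names no other, and permits an intercept alone.

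Three stronger readings are tempting and are not supported.

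- A reader might infer that the month-4 error is definitely too wide. It is so only if correlation fades with time, and the documents give no correlation or variance.
- A reader might infer that month 12 is anticonservative under the whole permitted family. It is too narrow only without a slope. In the simulated trials AIC chose intercept plus slope 95-100% of the time, and month 12 is then slightly conservative. Month 12 is also secondary.
- A reader might infer that the per-visit group differences are affected. Those use the separate site-only model, in which within-patient correlation plays no part. Even in the longitudinal model, an intercept-only fit gives a ratio of 1.00 for the difference at a visit when variances are equal.

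The power loss is also negligible if the effect is as large as the 0.77 used for sizing; the 0.35 SD effect is my assumption. Limitations does concede, however, that this effect size was carried over from much earlier delivery of ICU-VR.

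**Conclusion.** The point holds in conditional form. The named family is restrictive for this schedule, and one permitted member, an intercept alone with independent residuals, can produce false positives. Under the assumed fading, type I error is about 10-14% at month 12, and about 6-9% at month 6 if only months 3, 4 and 6 are fitted. Intercept plus slope is largely safe: month 4 is 6-25% too wide and other visits are within about 7%, with power lost only for effects well below 0.77 SD. The sizes rest on fading correlation, independent residuals, equal variances, complete data and a contrast of change from month 3. The remark on site slopes needs no assumption about within-patient correlation. This is a modest weakness that is cheap to remove, not an error that invalidates the primary comparison.

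**What to change.** For the continuous scores, replace the random-effects clause with:

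- visit as a categorical factor, with visit-by-arm terms;
- an unstructured within-patient covariance over the five scheduled visits, fitted by REML with Kenward-Roger or Satterthwaite degrees of freedom;
- a named fallback if it does not converge, for example heterogeneous Toeplitz, then spatial power on months.

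At minimum, rule out the intercept-only model with independent residuals. Drop the random slope for site. Fixed rather than random site intercepts are optional. The logistic models for the cut-off outcomes need their own wording, which this change does not supply.

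The cost is a change of text and of the model call. The covariance has 5 × 6/2 = 15 parameters instead of 2 to 4, which five fixed visits and 64 to 80 patients can support. The small risk of non-convergence is covered by the fallback.
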